### Recruitment

Participants referred to the IPP will be contacted to receive an overview of the study, have their questions addressed, and provide verbal consent for participation. Interested participants will then complete a pre-screening survey via Research Electronic Data Capture (REDCap) to determine preliminary eligibility. Individuals responding to social media advertisements or flyers will be directed to REDCap via the link provided in the advertisements to complete the same pre-screening survey. For those who meet initial eligibility criteria, a screening visit over the phone will be scheduled to assess full eligibility. The screening visit will include an eligibility review, collection of demographic data, medical history, confirmation of MDD diagnosis, and completion of an FES safety questionnaire. Verbal informed consent will be obtained before screening, and written informed consent will be obtained on the first day of on-site intervention sessions.

While there are no known risks of FES stimulation to ova or fetuses during pregnancy, the possibility of unknown risks cannot be entirely ruled out. Thus, female participants will be asked to confirm they are not pregnant or planning a pregnancy during the study. Upon meeting all requirements, a baseline visit will be scheduled.

### Randomization and masking

Participants will be randomly assigned in a 1:1 ratio to receive either active FES or sham using a randomization schedule generated through a secure REDCap module. Block randomization, stratified by sex, will account for potential differences in response and tolerability. Personnel conducting outcome assessments and other blinded study procedures will not have access to the fixed block size or treatment assignments. Randomization will be conducted by the intervention staff, who will have access to group assignments as required to deliver and monitor the stimulation sessions. In an emergency, the study doctor may be informed of the participant’s group assignment if this information is necessary for clinical management.

Moreover, to preserve blinding, sensory and non-Duchenne-patterned sham stimulation will be utilized. Participants will be instructed to avoid interaction with one another throughout the study. Blinding effectiveness will be assessed after each session by asking participants and raters to indicate whether they believe the participant received active or sham FES.

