**Methods:**

This single-site, double-blind, randomized, sham-controlled pilot trial will enroll 60 participants to evaluate the therapeutic effects of 20 sessions of bilateral facial FES over four weeks. The study will assess the impact of FES on depressive symptoms, associated anxiety, quality of life, and sleep. Participant dropout and protocol adherence will be monitored to assess tolerability, while adverse events will be monitored to assess safety throughout the trial. Eligible participants will complete 20 on-site intervention visits and 6 online visits, including a screening visit, a baseline visit, and four post-stimulation follow-up visits.

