### Outcome measures and data collection

The primary outcomes include changes in depressive symptoms, measured by the HAM-D-17, a validated, semi-structured, clinician-administered interview for assessing the presence and severity of depression. The other primary outcome will assess tolerability and safety based on dropout, data completion, protocol adherence rates, and the frequency and nature of AEs and SAEs. Secondary outcomes include MDD response and remission rates, anxiety, quality of life, and sleep quality. These outcomes will be measured using the 16-Item Quick Inventory of Depressive Symptomatology – Short Form (QIDS-SR-16) [25], Generalized Anxiety Disorder-7 (GAD-7) [26], World Health Organization-5 Well-Being Index (WHO-5) [27], and Pittsburgh Sleep Quality Index (PSQI) [28]. Additional secondary outcomes include response (50% decrease in total HAM-D-17 score) and remission (HAM-D-17 < 7) rates and sustainability of these outcomes for up to 28 days post-stimulation. In addition, facial expressivity during video-recorded emotional recall interviews will be assessed as an exploratory outcome.

An independent assessor will administer the HAM-D-17 and complete the Concomitant Medication Record (CONMED) at baseline, at the end of each week during the randomized intervention period, and at each follow-up visit. Participants will also be queried daily about their experiences and any AEs or SAEs they may encounter. To monitor participant burden, an FES Experience assessment will be conducted at the end of each treatment week through REDCap. All secondary outcomes will be assessed at baseline, at the end of each week during the randomized intervention period, and during follow-up visits using REDCap. Emotional recall interview will be administered at baseline and at the end of each week during the intervention period.

This study will also collect necessary personal health information, including the participant’s name, date of birth, medical records (new or existing) related to psychiatric or medical conditions, current and past medications, surgical implants, and any illnesses or psychiatric procedures that could affect study participation. This information will be obtained from the participant, their physician, or their medical records.

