### Patient retention and adherence

To develop professional relationships with participants, a specific research team member will be assigned to each participant for consistency across all visits. Participants will receive $30 for each on-site visit. Participants are allowed to miss up to two intervention visits during the intervention period. Missed visits will be recorded as non-adherent in the database and rescheduled immediately after the planned intervention period so that participants can complete all treatment sessions without substantial delay.

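### Unblinded intervention staff randomise with a fixed block size within sex, so they could foresee part of the sequence; the one-team-member rule also needs squaring with the blinded assessor

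*Protocol article*

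**What the plan says.** The protocol article (Randomization and masking) describes the allocation as follows.

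- Generation: "Participants will be randomly assigned in a 1:1 ratio to receive either active FES or sham using a randomization schedule generated through a secure REDCap".
- Restriction: "Block randomization, stratified by sex, will account for potential differences in response and tolerability".
- Who is kept from it: "Personnel conducting outcome assessments and other blinded study procedures will not have access to the fixed block size or treatment assignments".
- Who does it: "Randomization will be conducted by the intervention staff, who will have access to group assignments as required to deliver and monitor the stimulation sessions".

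The Abstract gives the setting: "This single-site, double-blind, randomized, sham-controlled pilot trial will enroll 60 participants". Two later sections bear on rater blinding. Outcome measures and data collection says "An independent assessor will administer the HAM-D-17", at baseline, at the end of each intervention week and at each follow-up. Patient retention and adherence says that "a specific research team member will be assigned to each participant for consistency across all visits".

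**The concern.** Concealment requires that whoever can affect a participant's entry cannot tell which arm comes next. Here the block size is fixed, and the only people barred from it are the blinded personnel. The people who carry out the randomisation know every assignment made so far. With one site and one stratification factor there are just two running sequences, one per sex, and both are in full view of this team. If they were not told the block size, they could work it out as the sequence grows. REDCap may hide the next entry, but it cannot stop that inference.

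If such staff can affect when someone enters, or whether someone is excluded at a late check, the arms may differ at entry in ways that adjustment for baseline HAM-D-17 and sex does not remove. The trial is meant to supply a signal for a multisite trial, so avoidable selection bias would weaken its main use.

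A second, smaller matter is the retention rule. One person at all visits sits awkwardly with a clinician-rated primary efficacy outcome that depends on an assessor who does not know the arm.

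**Working it through.** **Inputs.** From the article: 1:1 allocation, fixed blocks, stratification by sex, one site, 60 participants, and randomisers who know past assignments. The block size is not stated. I assume sizes 2, 4, 6, 8 and 10 and show the range. The article states no predictability figure, so there is none to reproduce.

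**Share certain in advance.** Write the block size as 2m, with m places per arm. An allocation is certain once one arm's places are used up. The expected number of certain allocations per block is 2m/(m+1), a share of 1/(m+1).

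Check for size 4 (m = 2), which has six possible sequences. In AABB and BBAA the last two places are certain. In the other four sequences only the last place is certain. The mean is (2×2 + 4×1)/6 = 8/6 = 1.33 per block, and 1.33/4 = 33.3%.

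**Best-guess accuracy.** The guess is always the arm with more places left. For size 4 the chances of being right at the four positions are 1/2, 2/3, 2/3 and 1. The sum is 2.833, and 2.833/4 = 70.8%. The other sizes follow from the same recursion over the places left.

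| Assumed block size | Certain per block | Share certain | About, of 60 | Best guess right |
|---|---|---|---|---|
| 2 | 1.00 | 50.0% | 30 | 75.0% |
| 4 | 1.33 | 33.3% | 20 | 70.8% |
| 6 | 1.50 | 25.0% | 15 | 68.3% |
| 8 | 1.60 | 20.0% | 12 | 66.6% |
| 10 | 1.67 | 16.7% | 10 | 65.3% |

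These figures suppose that the block size is known throughout, and they ignore an unfinished last block in each sex. A team that first had to infer the size would foresee somewhat less.

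**Where foreknowledge could act.** The Recruitment section places the full eligibility review at a phone screening visit and schedules baseline only once requirements are met. Study design and setting makes both of those visits remote. Eligibility criteria, however, lists an exclusion for people in whom FES cannot produce a Duchenne smile. That needs the device, so it cannot be judged remotely, and the only on-site visits listed are the 20 intervention visits. The article does not say who judges it, at which contact, or whether before randomisation. If it follows randomisation, a person excluded there before any session would also drop out of the modified intention-to-treat set (Data analysis plan), which requires at least one FES session.

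**The team-member rule.** All visits means 20 on-site stimulation visits plus 6 remote ones, 26 in total. HAM-D-17 ratings fall at baseline, at the end of each intervention week and at each follow-up. The primary contrast runs from baseline to day 20, so the ratings that matter most for it are baseline and the last one of the intervention period. Read literally, one person attends both stimulation and rating visits. The article gives that person no stated role.

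**The case against.** The strongest reply is that foreknowledge biases a trial only if its holder can influence entry, and the article does not show that these staff can. Screening is a REDCap survey and a phone visit, and nothing says that intervention staff screen, enrol or time entry. Who prepares the table and exactly when allocation occurs are details an article may leave to the full protocol. This stands as a limit: the route to bias is possible but not documented. It does not remove the point, because the article itself states a fixed block size and unblinded randomisers. That is a weak arrangement as described, not merely one that is described too briefly.

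Three stronger readings are tempting, and the documents do not support them.

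- A reader might infer that the intervention staff can predict the allocations outright. Unless the block size is 2, most allocations are not certain, and even then only half are.
- A reader might infer that they alone can judge the FES-smile exclusion. The article names nobody for that decision.
- A reader might infer that the retention rule breaks the separation of raters from treatment. Assessors are expressly said to be people who "will not have access to the fixed block size or treatment assignments", and a contact person or coordinator who does no ratings would fit every section. What remains is an inconsistency of wording.

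It is also fair to say that the table measures how guessable the sequence is. It shows no effect on the HAM-D-17 contrast.

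**Conclusion.** The concern holds as partial predictability of the allocation to the people who perform it. Across assumed block sizes of 10 down to 2, about 17% to 50% of allocations (roughly 10 to 30 of 60) are certain in advance, and best-guess accuracy is about 65% to 75%. This rests on an undisclosed block size and on staff who know it or infer it. Whether it biases entry depends on two facts the article does not give: whether these staff influence enrolment timing or the device-dependent exclusion, and whether that exclusion comes before randomisation. Nothing suggests that allocation has been subverted. The scheme should be changed because the weakness is avoidable and recruitment is planned to run to June 2028. The team-member rule is a secondary point that calls for clarification only.

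**What to change.** For the remaining participants:

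- Load a REDCap allocation table with randomly varying block sizes within sex, prepared by someone outside the intervention team and hidden from that team.
- State that randomisation is carried out only after all eligibility criteria, including the FES-smile criterion, and the baseline ratings are recorded.
- Limit the single team member in Patient retention and adherence to non-rating contact. State that nobody who delivers or monitors stimulation performs or attends a HAM-D-17 rating, including the weekly ratings during the intervention period.

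Cost: an ethics board amendment, since recruitment has begun, and a new table for the slots not yet used. Possible imbalance at the end is slightly larger, and a block left unfinished at the changeover can add to it. No extra rater is needed, because an independent assessor is already planned. Varying blocks reduce predictability without removing it, because the same unblinded staff still see past assignments. That is why the rule on the timing of randomisation belongs with the new table.

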### Intervention

Participants will receive transcutaneous FES targeting the bilateral zygomaticus major and orbicularis oculi muscles with self-adhesive surface electrodes placed on all four muscles (Fig 3). Each FES session, whether active or sham, will last for 60 minutes, comprising 15 minutes of preparation and 45 minutes of stimulation. FES will be administered using the Twin Stim® Plus Digital TENS/EMS FES device (Health Canada License name: TWIN STIM SERIES), providing 300 μs charge-balanced biphasic pulses at 40 Hz. During the intervention sessions, participants will watch a comedy video designed to elicit genuine Duchenne smiles while being instructed to intentionally produce a Duchenne smile at least once per minute. All intervention visits will be video recorded.

**Fig 3 pone.0357381.g003:**
[figure not shown]
Surface electrode placement. FES of bilateral zygomaticus major and orbicularis oculi muscles.

For the active group, a synchronized stimulation of four muscles (i.e., the bilateral zygomaticus major and bilateral orbicularis oculi) will be delivered. The current amplitude will range from 8 to 15 mA, which is sufficient to induce contractions in the desired target muscles, with alternating 15-second periods of stimulation and rest. These parameters align with previous FES studies for muscle activation [24]. If participants experience discomfort, the stimulation intensity may be adjusted within permitted parameters, and all adjustments will be documented.

Participants in the sham arm will receive FES with identical parameters, except that the stimulation will be limited to sensory levels (1–8 mA) and will follow a random circulating pattern rather than a Duchenne pattern. Although sham stimulation may cause some muscle contractions, it does not affect the study’s primary focus on examining the effects of Duchenne-pattern stimulation on mood.

### Outcome measures and data collection

The primary outcomes include changes in depressive symptoms, measured by the HAM-D-17, a validated, semi-structured, clinician-administered interview for assessing the presence and severity of depression. The other primary outcome will assess tolerability and safety based on dropout, data completion, protocol adherence rates, and the frequency and nature of AEs and SAEs. Secondary outcomes include MDD response and remission rates, anxiety, quality of life, and sleep quality. These outcomes will be measured using the 16-Item Quick Inventory of Depressive Symptomatology – Short Form (QIDS-SR-16) [25], Generalized Anxiety Disorder-7 (GAD-7) [26], World Health Organization-5 Well-Being Index (WHO-5) [27], and Pittsburgh Sleep Quality Index (PSQI) [28]. Additional secondary outcomes include response (50% decrease in total HAM-D-17 score) and remission (HAM-D-17 < 7) rates and sustainability of these outcomes for up to 28 days post-stimulation. In addition, facial expressivity during video-recorded emotional recall interviews will be assessed as an exploratory outcome.

An independent assessor will administer the HAM-D-17 and complete the Concomitant Medication Record (CONMED) at baseline, at the end of each week during the randomized intervention period, and at each follow-up visit. Participants will also be queried daily about their experiences and any AEs or SAEs they may encounter. To monitor participant burden, an FES Experience assessment will be conducted at the end of each treatment week through REDCap. All secondary outcomes will be assessed at baseline, at the end of each week during the randomized intervention period, and during follow-up visits using REDCap. Emotional recall interview will be administered at baseline and at the end of each week during the intervention period.

This study will also collect necessary personal health information, including the participant’s name, date of birth, medical records (new or existing) related to psychiatric or medical conditions, current and past medications, surgical implants, and any illnesses or psychiatric procedures that could affect study participation. This information will be obtained from the participant, their physician, or their medical records.

### Data management, confidentiality, and monitoring

REDCap will be used as the primary platform for data collection in this study. Participants will complete self-report questionnaires through REDCap links sent on a daily and weekly basis. Clinician-administered assessments (i.e., MINI, HAM-D-17, and MADRS) will be conducted by trained study staff. All data will be securely stored on the REDCap server and linked with a unique identifier for analysis. The screening survey will collect personally identifiable information, whereas the REDCap forms used for outcome assessments will use only a unique study identification number. Personally identifiable information will be kept confidential in accordance with applicable privacy legislation, including Ontario’s Personal Health Information Protection Act (PHIPA).

Video recordings, which contain identifiable facial and voice information, will be stored on a secure, password-protected hard drive within the Unity Health Toronto environment, accessed only by authorized study personnel, and processed locally using OpenFace; only coded numerical facial-movement data linked to study identification numbers will be used for analysis, and no recordings will be uploaded to external websites, cloud services, or third-party servers.

To assess data quality, a second reviewer will verify the data from a randomly selected 10% of participants. Screening data from individuals who are found to be ineligible will be retained unless they request their removal, provided that the data have not already been anonymized or incorporated into aggregate analyses. All study records will be stored securely for seven years in accordance with institutional research ethics requirements.

### Safety and adverse events monitoring

Participant safety during all FES sessions will be overseen by trained investigators, with a licensed physician available at every visit. All AEs will be systematically recorded, including their severity, causality, and outcomes. AEs will be assessed daily: 1) the severity of each AE will be graded as mild, moderate, or severe, 2) causality will be categorized as probable, possible, unlikely, not related, or unclassified. SAEs are defined as events leading to significant disability, death, congenital defects, hospitalization, or requiring intervention to prevent such outcomes. Any SAE will be reviewed immediately and reported in accordance with ethical guidelines.

The outcome of each AE will be recorded as recovered/resolved, recovering/resolving, not recovered/not resolved, recovered/resolved with sequelae, fatal, or unknown. The study physician will promptly evaluate any unexpected events requiring urgent attention. In the event of an AE, medical care will be facilitated for the participant, and follow-up will be conducted by the Principal Investigator (PI). The PI will review and initial the AE log within 72 hours of its completion. All AEs, regardless of their relationship to FES, will be documented, followed until adequate resolution, and graded for severity and causality.

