### Eligibility criteria

Recruitment will take place through referrals to the Interventional Psychiatry Program (IPP) at St. Michael’s Hospital, Unity Health Toronto, as well as through approved advertisements and flyers. Sixty participants with unipolar, non-psychotic MDD, as determined by the Mini-International Neuropsychiatric Interview (MINI) [21], will be recruited. Eligible participants will be males and females aged 18–70 years. They must have a Montgomery–Åsberg Depression Rating Scale (MADRS) [22] score of ≥7 and no more than two failed treatment trials during the current major depressive episode. Eligible participants will be required to maintain a stable regimen of medication and psychotherapy for at least four weeks before the study, and have no plan to change them throughout the intervention period, and during the follow-up, as reported in the Antidepressant Treatment History Form (ATHF) [23].

Individuals will be excluded if they have received ECT, magnetic seizure therapy, or intravenous ketamine during the current depressive episode, or rTMS within the previous 28 days. Additional exclusion criteria encompass a diagnosis of fibromyalgia, a history of epilepsy or seizures, oral metallic orthopedic implants, or damaged or dysfunctional facial nerves. Psychiatric comorbidities warranting exclusion consist of past or present symptoms of mania, hypomania, mixed episodes, psychotic disorders, obsessive-compulsive disorder, post-traumatic stress disorder, active substance use or dependence (excluding nicotine and caffeine), neurodegenerative disorders, or dementia. Participants with current suicidal intent or plan (MADRS item 10 score ≥ 4) or inability to generate the Duchenne smile with FES will also be excluded. Additionally, individuals who do not speak English will be excluded from this RCT to ensure clear comprehension of study information, facilitate communication for addressing participant questions, and obtain informed consent effectively.

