### Participant withdrawal and study termination

Participants may withdraw their consent and discontinue the study at any time without penalty. Withdrawal may also be initiated by the participant’s physician or the investigator if continued participation is deemed to pose a significant risk. Discontinuation criteria include a worsening of depression (defined as a more than 25% increase in QIDS-SR-16 score compared to baseline across two consecutive assessments), developing active suicidal intent, attempting suicide, non-adherence to study procedures, or missing more than two FES sessions. Participants meeting exclusion criteria during the trial will also be withdrawn. All early withdrawals will be documented, and participants will be asked to provide feedback on their FES experience and undergo any recommended medical evaluations. If study termination or early withdrawal is due to an AE or SAE, the research team will assist the participant in obtaining appropriate medical care, and the PI will conduct follow-up as required.

The study will be paused if SAEs related to FES are identified. Premature termination may occur if significant risks to participants, protocol non-adherence, insufficient evaluable data, or device modifications are identified. In such cases, the research ethics board will be informed.

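### The SAE definition is a closed list with no life-threatening or medically important limb, so a suicide attempt or seizure needing neither admission nor preventive intervention stays outside the SAE count and the pause rule

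*Protocol article*

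**What the plan says.** The definition is in the protocol article under Safety and adverse events monitoring: "SAEs are defined as events leading to significant disability, death, congenital defects, hospitalization, or requiring intervention to prevent such outcomes". SAE status then matters in three places.

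- **Review and reporting** (same section): "Any SAE will be reviewed immediately and reported in accordance with ethical guidelines".
- **Outcome** (Outcome measures and data collection): tolerability and safety form one of the primary outcomes, which includes "the frequency and nature of AEs and SAEs". The Objectives section also puts SAE incidence into the primary hypothesis.
- **Pause** (Participant withdrawal and study termination): "The study will be paused if SAEs related to FES are identified".

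Other provisions do not depend on SAE status. AEs are assessed daily. "All AEs, regardless of their relationship to FES, will be documented, followed until adequate resolution, and graded for severity and causality". "The study physician will promptly evaluate any unexpected events requiring urgent attention". For the log, "The PI will review and initial the AE log within 72 hours of its completion".

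Two events get special treatment elsewhere. Eligibility criteria excludes people with "a history of epilepsy or seizures". Participant withdrawal and study termination names a suicide attempt as a discontinuation criterion, and also withdraws anyone who comes to meet an exclusion criterion during the trial.

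**The concern.** The definition works by consequence only. If an event caused no death, disability, birth defect or admission, and needed no intervention to avert one of these, it is not serious, however alarming it was. Nothing lets an event qualify because it put life at risk or because a clinician judged it important.

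The two events that best test this are foreseeable here. All participants have MDD, and entry is barred for suicidality only at the level of intent or plan (MADRS item 10 of 4 or more), so lesser ideation can be enrolled. The intervention is electrical stimulation of the face, and seizure history is considered important enough to exclude. Either event could end a participant's trial and still be logged as an ordinary AE.

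At stake are the accuracy of the SAE count in a primary outcome and whether the only stated pause rule can respond to a device-related seizure.

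**Working it through.** No formula applies to the main point, and the article gives no figure to reproduce. The check takes the definition limb by limb and applies it to a suicide attempt or a new seizure.

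**Step 1. Is the event an SAE as defined?**

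| Case | Admission | Intervention needed to avert death, disability or admission | Lasting harm | Classification |
|---|---|---|---|---|
| A | yes | any | any | SAE (hospitalization limb) |
| B | no | yes | no | SAE (preventive-intervention limb) |
| C | no | no | no | AE only |

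Case C covers, for example, a self-limiting seizure during a session or a suicide attempt that needed no treatment. Only case C supports the concern.

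**Step 2. What does case C lose?**

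| Provision | Depends on SAE status? | Case C, as written |
|---|---|---|
| Recording, follow-up and grading | no | applies |
| Prompt physician evaluation | no; event must be unexpected and urgent | applies if so |
| AE part of the primary outcome | no | counted |
| Guaranteed immediate review and reporting | yes | lost |
| SAE part of the primary outcome | yes | not counted |
| Study pause | yes, and must be related to FES | cannot be met |

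**Step 3. Which case C events could reach the pause rule under a wider definition?** The rule has two conditions: the event is an SAE, and it is related to FES.

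- Seizure during stimulation, graded probably related: the second condition is presumably met, and only the definition blocks the rule.
- Suicide attempt related to FES: the same.
- Suicide attempt unrelated to FES: the second condition fails, so the definition makes no difference.

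**Step 4. Is the second condition workable?** The causality scale runs from probable through possible and unlikely to not related, with an unclassified category. None of these is simply called related, and the article does not say which grades satisfy the pause rule. So one input to the rule is defined too narrowly and the other is not mapped to the scale that feeds it.

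**Step 5. Compare with the other sections.** A suicide attempt is a discontinuation criterion. A seizure during the trial gives the participant a seizure history, which is an exclusion criterion, and participants who come to meet one are withdrawn. On that natural reading both case C events end participation while being classed as non-serious.

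**Scale.** With 30 participants planned per arm, one event is 1/30 = 3.3%. Reclassifying one active-arm event would move that arm's observed SAE rate from 0/30 = 0% to 3.3%. This shows how coarse the count is. It does not estimate how often case C would occur, and the documents give no rate for that.

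**The case against.** The strongest reply is that the gap is small and other provisions already cover most of it. Much of this stands, and several stronger readings that a reader might infer are not supported.

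- **That every attempt or seizure without admission falls outside the definition.** It does not. The last limb takes in events that needed intervention to avert death, disability or admission, so a treated overdose can be an SAE without an admission.
- **That such events escape prompt review.** They do not. Sessions are directly monitored, a physician is available at every visit, AEs are assessed daily, and urgent unexpected events are promptly evaluated. The 72-hour limit is a sign-off deadline for the log, not the first clinical response, and is not an error. What is lost is the guaranteed SAE-level review and reporting.
- **That the same participant could receive up to three more sessions before the log is reviewed.** The withdrawal provisions point the other way for both events.
- **That the event vanishes from the primary outcome.** It still counts as an AE, with severity and causality grades. Only the SAE count omits it.
- **That a wider definition would pause the study after any suicide attempt.** An attempt unrelated to FES would not do so under any SAE definition.

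It is also fair to say that discontinuation does not by itself imply seriousness, since missed sessions are a discontinuation criterion too. The mismatch is therefore one of weight rather than a literal contradiction. The article also allows termination for significant risk without reference to SAE status, but that is discretionary.

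Finally, the article condenses a full protocol (S2 File) that is not shown and may hold a fuller definition. That would excuse an omission, but the article does not omit the definition. It states one, and the stated one is too narrow. If S2 File is wider, the article misreports it and needs correcting.

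**Conclusion.** The point holds in its narrow form. As worded, a suicide attempt or seizure with no admission, no preventive intervention and no lasting harm is an AE only. It lacks guaranteed immediate SAE review and reporting, is absent from the SAE count, and cannot meet the pause rule even when related to FES. The related seizure is the clearest case, because only the definition stands in the way. This fits poorly with the weight given to the same events under Eligibility criteria and under Participant withdrawal and study termination.

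The consequence is one of classification. Its frequency cannot be derived from the documents and is probably low. In arms of 30, however, one event settles whether an arm reports any SAE at all.

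The conclusion assumes that the sentence is applied as written and that the list is exhaustive, as its phrasing indicates. It also rests on reading a new seizure as meeting the seizure-history exclusion; without that reading, the mismatch remains for suicide attempts. The change should be made, but the point does not threaten the trial's validity.

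**What to change.** Amend the definition under Safety and adverse events monitoring to include life-threatening events and medically important events. Reconcile it with Eligibility criteria and with Participant withdrawal and study termination, so that the classification of suicide attempts and new seizures is explicit. State which of the causality grades count as related in the pause rule; that choice is for the sponsor and the ethics board. If S2 File already contains these elements, correct the article to match it.

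The cost is about one paragraph of amendment and a change to the AE form, with possibly a few more expedited reports. Recruitment began in June 2026, so an early change keeps classification consistent across participants. Any events already logged should be checked against the amended wording.
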